**Figure 1 F1:**
[figure not shown]
Diagrammatic representation of observation time for an individual in the proposed self-controlled case series design. MI, myocardial infarction; UTI, urinary tract infection.

Individuals can have more than one UTI during the observation period, and therefore can have more than one 90-day risk period. Where risk periods overlap, the later period takes precedence, and the earlier period is shortened. There will be a prerisk period of 7 days before the risk period, to allow for the situation where an individual has an UTI for several days prior to consultation, so events in the prerisk period are not erroneously attributed to the baseline period.

Baseline periods are all times outside of the risk and prerisk periods. The study period is from 1 January 2010 to 31 December 2020. The observation period is different for each individual. It generally follows the study period but may start later for some individuals who were not Welsh residents at the start of the study period but became so later, or who turned 30 years of age sometime during the study period. Similarly, the observation period may end before the study period when individuals moved out of Wales or died.

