## Introduction

Since the late 1990s, an increasing number of observational studies have found an association between acute infections and myocardial infarction (MI).^1–10^ Most studies focused on respiratory tract infections (RTIs), and found an increased risk of acute MI in the 1–3 days following an RTI, with the effect size varying according to the infecting organism.^2–8^ For example, Kwong *et al* found a sixfold increase in the risk of MI in the week after influenza infection, a fourfold increase after respiratory syncytial virus and a threefold increase after other respiratory viruses.^5^ Several studies have also found evidence of an association between pneumonia and acute cardiovascular events (including MI and stroke).^9–13^ The increased risk of acute cardiovascular events following pneumonia infection persists for up to 10 years.^9^ This long-term risk of acute cardiovascular events has also been observed after other severe infections, including sepsis and bacteraemia.^14–17^

It is thought that acute infection may cause major cardiovascular events through three mechanisms. First, the inflammatory response from acute infection may destabilise atherosclerotic plaques. Second, the prothrombotic, procoagulant state associated with acute infection may increase the risk of thrombosis at the site of plaque disruption. Third, inflammation and fever lead to an increase in heart rate, which may cause ‘demand ischaemia’ if the metabolic demands of the myocardial cells exceed oxygen supply.^1^

Urinary tract infections (UTIs) can affect any part of the urinary system, including the kidneys, ureters, bladder and urethra. Most infections involve the lower urinary tract: the bladder and the urethra. UTIs are common infections, with 37% of women reporting experiencing at least one in their lifetime, and 29% experiencing more than one.^18^ UTIs are associated with considerable morbidity. The global burden of disease study 2010 estimates the disability-adjusted life-years attributable to tubulointerstitial nephritis, pyelonephritis and UTI to be 45 (95% uncertainty interval 32–55) per 100 000 population.^19^

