## Methods and analysis

### Aims and objectives

The specific objectives of this research are to:

Estimate incidence rate ratios (IRRs) for acute MI and stroke in the 90 days following a clinically suspected and microbiologically confirmed UTI compared with baseline (all times outside of the 90-day risk period).Assess the effect of different methods of UTI ascertainment on estimated rate ratios (ie, clinically suspected and microbiologically confirmed; clinically diagnosed only; clinically suspected but not supported by microbiology and UTI diagnosed and treated in hospital).Investigate whether the effect of a clinically suspected and microbiologically confirmed UTI on acute MI and stroke differs according to the infecting organism.

Our primary hypothesis is that a clinically suspected and microbiologically confirmed UTI will increase the risk of acute MI or stroke in the 0–90 days postinfection period.

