	As both MI and stroke have relatively high death rates, the length of the observation period is dependent on events, and no further exposures are possible after death.	Use an event-dependent observation period model extension^38^ and conduct a sensitivity analysis that repeats the analysis, excluding individuals who died within 30 days of the event.	Bruer *et al* used the event-dependent observation period model extension in their study on the association between antipsychotic drugs and myocardial infarction.^39^ Langan *et al* studied the risk of stroke following herpes zoster. They conducted a sensitivity analysis excluding individuals who died within 90 days of stroke.^40^
Event rates are constant within defined periods	MI and stroke are more common in older individuals and may be affected by seasonal changes.	Control for age and season effects.	Grave *et al* studied the association between seasonal influenza vaccination and Guillain-Barré syndrome. They adjusted for calendar month, as the vaccinations are seasonal by design.^41^ In a study of the association between chickenpox and stroke, Thomas *et al* adjusted for age in 5-year age bands.^42^
Events are independently recurrent or rare.	MI and stroke are not independent: once an individual has a first event, they are more likely to have a second.	Study first events only.	Langan *et al* began the observation period 12 months into follow-up time to ensure first stroke events had been correctly identified.^40^

MI, myocardial infarction; UTIs, urinary tract infections.

A diagrammatic representation of observation time for an individual in the proposed SCCS design is given in figure 1. Risk periods start on the date of an UTI and end 90 days later. The date of an UTI is the earliest date of occurrence of any of the events necessary for each different UTI definition. For example, the definition of UTI in our primary analysis is a combination of an UTI-related diagnostic code and antibiotic prescription in WLGP data and a urine culture result that supports a diagnosis of UTI in the WRRS data, occurring within a 7-day window. In this case, the date of the UTI would be the date of whichever of the following events occurred first: UTI-related diagnostic code, antibiotic prescription, supporting urine culture.

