### Exposure

The exposure of interest is an UTI. The risk period is 0–90 days following an UTI. This period was chosen as previous research has shown an increase in acute MI and stroke risk in the 1–90 days following an UTI.^6^ There will be a prerisk period of 7 days before the risk period, to allow for the situation where an individual has an UTI for several days prior to consultation, so events in this period are not erroneously attributed to the baseline period. Individuals can be exposed to an UTI more than once during the observation period. Each exposure will be followed by the same 90-day risk period. Baseline periods are all other times.

To ascertain UTI, we developed definitions that reflected the Public Health Wales Microbiology Division’s standard operating procedure for the investigation of urine.^36^ These procedures are followed by NHS microbiology laboratories across Wales. For each definition, the data sources required and the clinical scenario represented is summarised in table 2, and the code lists used are given in online supplemental material B–D. In our primary analysis, an individual will be regarded as being exposed to an UTI if the following events occur within a 7-day window:

A General Practice (GP) record of an UTI diagnostic or symptom code.A GP record of an antibiotic prescription.A microbiology record of a urine sample with bacterial growth of a single organism of ≥1x10^8^ colony-forming units (CFU) per litre and white cell count (WCC)≥1x10^8^/L. If there are two organisms grown, both must demonstrate growth of ≥1x10^8^ CFU per litre. More than two organisms will be regarded as mixed growth and thus not supportive of an UTI diagnosis. In a sensitivity analysis, we will widen the microbiological criteria and include all urine samples with bacterial growth of a single organism of ≥1x10^7^ CFU per litre, irrespective of the WCC.

**Table 2 T2:** Definitions of UTI for primary and secondary analyses. As the UTI definitions are combinations of two or more components, the start of the risk period is defined as the date of the earliest component

	UTI-related read code in GP data (online supplemental material B)	Antibiotic prescription in GP data (online supplemental material C)	UTI-related ICD-10 code in PEDW (online supplemental material D)	Urine culture results in WRRS	Time frame	Clinical scenario

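### All time after day 90 counts as baseline and no interval beyond it is reported or tested; if UTI risk outlasts 90 days the IRRs are pulled modestly toward 1

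*Protocol article*

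**What the plan says.** The Study design section of the Protocol article sets the window: "Risk periods start on the date of an UTI and end 90 days later". The text under Figure 1 defines the reference: "Baseline periods are all times outside of the risk and prerisk periods". The Exposure section repeats it for every UTI: "Each exposure will be followed by the same 90-day risk period. Baseline periods are all other times". The first objective likewise takes time outside the 90-day window as the comparator.

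The reason given for the length, in the Exposure section, is that "previous research has shown an increase in acute MI and stroke risk in the 1–90 days following an UTI".

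Under Statistical analysis, the last interval to be reported is days 29–90. Under Sensitivity and subgroup analyses, the only window whose length changes is the prerisk period, from 7 to 14 days. Table 1 handles the constant-rate assumption through age and season only.

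On duration of risk, the Introduction says of pneumonia: "The increased risk of acute cardiovascular events following pneumonia infection persists for up to 10 years". It adds that long-term risk "has also been observed after other severe infections, including sepsis and bacteraemia". UTI is not named in either statement.

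**The concern.** In a self-controlled case series, the IRR is only as good as the reference rate. If risk falls slowly after a UTI, some post-day-90 time is still raised-risk time. It then sits in the denominator and lowers every IRR.

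Evidence of raised risk in days 1–90 supports a window at least that long. It does not say where the excess ends. The authors protect the reference on the other side of the UTI, with a prerisk period whose length they test, but do nothing comparable after day 90.

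The assumption matters most for secondary analyses 4 and 5. These bring in hospital-diagnosed UTI, where more severe infection is plausible, and they use the same cut-off. The second objective compares IRRs across UTI definitions. If the excess lasted longer under one definition than another, a common cut-off would attenuate them unequally. The article also says an association would support funding for a later trial, so a loss of signal has a cost.

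**Working it through.** **1. The article's own power figure.** Inputs from Sample size and power: 51 656 MI and 58 146 stroke cases, 10% exposed (p = 0.10), 90-day window, IRR ρ = 1.3, alpha 0.05 (two-sided assumed). The observation length T used by the authors is not stated, so it is varied. Sex-weighted means from Summary of cases are about 3151 days (MI) and 2888 days (stroke). The full study period is 4018 days.

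Signed-root likelihood-ratio formula, with r = 90/T and β = ln ρ:
- D = ρr + 1 − r
- w = pD / (1 + pr(ρ − 1))
- A = 2w[ρrβ/D − ln D]
- B = (β²/A) · w · ρr(1 − r)/D²
- power = Φ[(√(nA) − 1.96)/√B]

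MI at T = 3151: r = 0.0286, A = 0.000227, B = 1.083, √(nA) = 3.425, so power = Φ(1.465/1.041) = 92.0%.

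| | T (days) | Power |
|---|---|---|
| MI | 3151 | 92.0% |
| MI | 4018 | 85.1% |
| Stroke | 2888 | 96.1% |
| Stroke | 4018 | 88.9% |

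The stated 90% at IRR 1.3 is reproduced for a plausible T.

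**2. Effect of carry-over.** Let c be the rate ratio after day 90 and f the share of reference time that it affects:

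observed IRR = true IRR / (1 + f(c − 1)).

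The article gives neither the size nor the duration of any such effect, so c = 1.1–1.3 and the durations are assumptions. T = 2981 days (the article's mean for female MI and male stroke cases), with one UTI per person at a random time and no age adjustment. True 90-day IRR = 1.30.

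| Carry-over lasts | f | c = 1.1 | c = 1.2 | c = 1.3 |
|---|---|---|---|---|
| 275 days (to day 365) | 0.09 | 1.29 | 1.28 | 1.27 |
| 1000 days | 0.29 | 1.26 | 1.23 | 1.20 |
| to end of observation | 0.50 | 1.24 | 1.18 | 1.13 |

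Examples: 1.30/(1 + 0.09 × 0.1) = 1.30/1.009 = 1.288, a fall of 0.9%. 1.30/(1 + 0.09 × 0.3) = 1.30/1.027 = 1.266, a fall of 2.6%. For carry-over to the end, 1.30/1.05 = 1.238 (4.8%) and 1.30/1.15 = 1.130 (13.0%).

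**3. Consequence for power.** Putting the attenuated IRR into the step 1 formula for MI at T = 2981, power is 93.3% with no carry-over and 91.5% for carry-over to one year at c = 1.1. For carry-over to the end of observation it is 79.7% at c = 1.1 and 58.1% at c = 1.2.

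**4. No effect.** If UTI has no effect at any time, c = 1 and the divisor is 1, so the IRR stays at 1. A purely late effect would push the 90-day IRR below 1, not above it.

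**5. What removing days 91–365 achieves against a multi-year tail.** Take T = 2796, one UTI at mid-observation, c = 1.2 to the end, and 91 + 7 = 98 risk and prerisk days.
- Unfixed: raised reference days are 1398 − 91 = 1307 of 2796 − 98 = 2698. The divisor is 1 + 0.2 × 1307/2698 = 1.097, and 1.30 reads 1.19.
- With days 91–365 removed: 1032 of 2423. The divisor is 1 + 0.2 × 1032/2423 = 1.085, and 1.30 reads 1.20.
- The new 91–365 level would itself read 1.2/1.085 = 1.11.

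The tail shows up in the new level but is hardly corrected.

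**The case against.** The strongest reply is that the documents contain no contradiction. The Introduction ties long-term risk to pneumonia, sepsis and bacteraemia, and notes that most UTIs involve the lower tract. The primary exposure is UTI suspected and treated in general practice. The one UTI-specific study cited found the highest risk in the first 3 days, and the 90-day window rests on that study. The comparator is stated openly and consistently. The bias is conservative, and small unless risk persists for years. All of this stands, and it keeps the point to a sensitivity analysis rather than a change to the primary model.

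A reader might infer more than the documents support:
- **That the Introduction shows the reference to be contaminated.** It does not say this of UTI.
- **That hospital UTI is bound to be attenuated more.** The article gives no figure for this, and Table 2 sets no severity criterion for secondary analysis 4. It holds only if that tail is longer or larger.
- **That nothing planned could hint at the problem.** A 29–90 day IRR still clearly above 1 would be a warning, though it would not measure what follows.
- **That attenuation could be drastic, for example with a lasting post-90-day ratio of 1.5 against a 90-day IRR of 1.30.** That needs risk to be higher after day 90 than before it, which does not fit a declining effect.

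What the objection does not answer is that the day-90 return to baseline is assumed, and its stated reason does not support it.

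**Conclusion.** The gap is real but modest. The article fixes day 90 as the point where reference time resumes, gives a reason that does not bear on what happens afterwards, and lists no analysis that would test it. It is an untested assumption, not an error or an inconsistency.

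If UTI risk stays raised, the IRRs move toward 1 by about 1–3% for carry-over to one year and about 5–13% only if it lasts to the end of observation. They do not move at all if there is no carry-over. A positive finding would not be undermined. A null or weak one would be harder to interpret.

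These sizes rest on assumed rate ratios of 1.1–1.3, one UTI per person at a random time, and no age adjustment. Repeat UTIs would change the affected share of reference time, in a direction that depends on their timing. Age adjustment may absorb part of a long tail.

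**What to change.** Keep the primary model. Add one item to the list under Sensitivity and subgroup analyses, for the primary UTI definition and secondary analyses 4 and 5: days 91–180 and 181–365 after each UTI enter as separate exposure levels, are removed from the reference, and have their IRRs reported. Where such an interval meets a later UTI's prerisk or risk period, the later UTI should take precedence, in line with the article's existing overlap rule. State the reading in advance: IRRs near 1 support the 90-day cut-off; if they are raised, the 90-day IRRs are reported as probably attenuated.

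**Cost.** No new data and two extra levels in an existing model. About 275 days per UTI leave the reference, which is 275/3251 = 8% to 275/2796 = 10% of mean observation. The loss of precision is small: with T = 2981, one UTI and IRR 1.30, the standard error of the log IRR rises by a factor √[(1/118.3 + 1/2608)/(1/118.3 + 1/2883)] = 1.002, where 118.3 = 91 × 1.3, 2883 = 2981 − 98 and 2608 = 2883 − 275, before age adjustment.

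**Limit.** The analysis detects a multi-year tail but does not fully correct it. A further level beyond day 365 would leave only time before the first UTI as reference. Table 1 warns that UTIs may rise after an MI or stroke, and the events of such cases fall in that pre-UTI time, so this reference concentrates event-dependent exposure bias. That level should be left out, or shown only as exploratory with this caveat.

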### Population

The SCCS method starts with identifying individuals who have had the outcome of interest. Therefore, the source population are individuals within the SAIL Databank who have a hospital admission record for acute MI or stroke during the study period. For inclusion, individuals will need to be aged 30–100 between 1 January 2010 and 31 December 2020 and be Welsh residents. We chose a lower age bound of 30 years to reduce the chance of including MIs and strokes due to congenital or other non-artherosclerotic causes. A lower age bound of 40 might reduce this chance further but would increase the chance of missing relevant events, especially given the greater burden of cardiovascular disease in Wales compared with the UK as a whole.^35^

### Outcomes

Outcomes of interest are acute MI or stroke, as identified by ICD-10 codes from inpatient diagnoses recorded in the PEDW. A list of ICD-10 codes to be used are given in online supplemental material A.

10.1136/bmjopen-2022-064586.supp1Supplementary data

### Exposure

The exposure of interest is an UTI. The risk period is 0–90 days following an UTI. This period was chosen as previous research has shown an increase in acute MI and stroke risk in the 1–90 days following an UTI.^6^ There will be a prerisk period of 7 days before the risk period, to allow for the situation where an individual has an UTI for several days prior to consultation, so events in this period are not erroneously attributed to the baseline period. Individuals can be exposed to an UTI more than once during the observation period. Each exposure will be followed by the same 90-day risk period. Baseline periods are all other times.

To ascertain UTI, we developed definitions that reflected the Public Health Wales Microbiology Division’s standard operating procedure for the investigation of urine.^36^ These procedures are followed by NHS microbiology laboratories across Wales. For each definition, the data sources required and the clinical scenario represented is summarised in table 2, and the code lists used are given in online supplemental material B–D. In our primary analysis, an individual will be regarded as being exposed to an UTI if the following events occur within a 7-day window:

A General Practice (GP) record of an UTI diagnostic or symptom code.A GP record of an antibiotic prescription.A microbiology record of a urine sample with bacterial growth of a single organism of ≥1x10^8^ colony-forming units (CFU) per litre and white cell count (WCC)≥1x10^8^/L. If there are two organisms grown, both must demonstrate growth of ≥1x10^8^ CFU per litre. More than two organisms will be regarded as mixed growth and thus not supportive of an UTI diagnosis. In a sensitivity analysis, we will widen the microbiological criteria and include all urine samples with bacterial growth of a single organism of ≥1x10^7^ CFU per litre, irrespective of the WCC.

**Table 2 T2:** Definitions of UTI for primary and secondary analyses. As the UTI definitions are combinations of two or more components, the start of the risk period is defined as the date of the earliest component

	UTI-related read code in GP data (online supplemental material B)	Antibiotic prescription in GP data (online supplemental material C)	UTI-related ICD-10 code in PEDW (online supplemental material D)	Urine culture results in WRRS	Time frame	Clinical scenario
Primary analysis	Yes	Yes	No	Yes, showing bacterial growth of ≥1x10^8^ CFU/L and WCC ≥1x10^8^ /L	Three codes occur within a 7-day window	GP clinically suspected and microbiologically confirmed UTI
Secondary analysis 1	Yes	Yes	No	Yes, showing mixed bacterial growth (any descriptor for ‘mixed growth’ or >3 organisms).	Three codes occur within a 7-day window	GP clinically suspected UTI with mixed growth
Secondary analysis 2	Yes	Yes	No	No	Same day	GP clinically diagnosed and treated UTI. It is important to consider this group as not all individuals with suspected UTI have urine culture, and limiting to those with culture is subject to selection bias.
Secondary analysis 3	Yes	Yes	No	Yes, showing bacterial growth of <1x10^7^ CFU/L.	Three codes occur within a 7- day window	UTI is clinically suspected but not supported by microbiology. This group is important to understand if early symptoms and signs of acute MI or stroke are attributed to UTI.
Secondary analysis 4	No	No	Yes	Yes, showing bacterial growth of ≥1x10^8^ CFU/L and WCC ≥1x10^8^ /L	Two codes occur within a 7-day window	UTI diagnosed and/or treated in hospital
Secondary analysis 5	Yes, OR ICD-10 code	Yes, OR ICD-10 code	Yes, OR: UTI Read code AND antibiotic Read code	Yes, showing bacterial growth of ≥1x10^8^ CFU/L and WCC ≥1x10^8^ /L	Two/three codes occur within a 7-day window	GP clinically suspected and microbiologically confirmed UTI or UTI diagnosed and/or treated in hospital

GP, General Practice; ICD-10, International Classification of Disease version 10; PEDW, Patient Episode Database for Wales; UTI, urinary tract infection; WCC, white cell count; WRRS, Welsh Results Reporting Service.

In secondary analysis 1, we will estimate the risk of MI and stroke among individuals with a GP record of an UTI code and antibiotic prescription, and a microbiology record of a urine sample with mixed bacterial growth (any descriptor for ‘mixed growth’ or >3 organisms). This is an important analysis given the uncertain clinical significance of mixed bacterial growth in an individual with symptoms of UTI. In secondary analysis 2, an individual will be regarded as exposed to UTI with only a GP record of a diagnostic or symptom code and an antibiotic prescription (no microbiology). Secondary analysis 3 will estimate the risk of MI and stroke among individuals where UTI was suspected and treated by the GP, but urine microbiology showed bacterial growth of<1x10^7^ CFU per litre (not supportive of an UTI diagnosis). Secondary analysis 4 will focus on individuals with a hospital admission with an UTI-related ICD-10 code and a microbiology record of a urine sample with bacterial growth of a single organism of ≥1x10^8^ CFU per litre and white blood cells ≥1x10^8^ per litre. As for the primary analysis, if there are two organisms grown, both must demonstrate growth of ≥1x10^8^ CFU per litre, and more than two organisms will be regarded as mixed growth. Secondary analysis 5 combines the primary analysis, and secondary analysis 4, considering individuals with either a GP record of an UTI code and antibiotic prescription, or a hospital admission with an UTI-related ICD-10 code, and a microbiology record of a urine sample with bacterial growth of a single organism of ≥1x10^8^ CFU per litre and white blood cells ≥1x10^8^ per litre. In the primary analysis, any hospital diagnosed UTI is likely to count towards baseline time, whereas they would be included in exposed time here.

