### Sensitivity and subgroup analyses

We will perform several sensitivity and subgroup analyses to assess the robustness of the findings of our primary analysis to different assumptions:

We will explore the impact of using a wider definition of MI and stroke, including ICD-10 codes for acute coronary syndromes and transient ischaemic attacks. This will include events that have potentially been missed by our main definition and assess how sensitive our findings are to the definition of MI and stroke.We will explore the impact of widening the microbiological definition of UTI to bacterial growth of a single organism of ≥1x10^7^ CFU per litre irrespective of WCC.We will differentiate first-ever MI or stroke from recurrent events, and report risk estimates separately. This analysis will exclude individuals with a PEDW record of an event before the observation period, and include only those who have their first ever event during the observation period.We will extend the prerisk period to 14 days. Some individuals may have had an UTI for several days prior to diagnosis, and so an acute MI or stroke during this time may relate to exposure but without a prerisk period, would count towards the baseline period.We will repeat the analysis excluding individuals who died within 30 days of an event to examine the potential effect of an event dependent observation period.We will restrict the definition of UTI to include only antibiotic prescriptions for nitrofurantoin (currently recommended first-line therapy) to explore whether the choice of antibiotic impacts the findings.We will use interaction terms to assess the impact of specific bacterial organisms on the relationship between UTI and MI or stroke.We will examine whether the COVID-19 pandemic may affect our findings by (1) excluding individuals whose MI or stroke occurred in 2020, and (2) including an interaction term to explore whether the association between exposure and outcome differs in 2020 vs pre-2020.We will include an interaction term to explore whether the association between exposure and outcome differs in those with and without a history of diabetes, given its potential role as a risk factor of both UTI and MI/stroke.

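### Mixed growth means more than two organisms in the primary rule but more than three in secondary analysis 1, and the 'widened' sensitivity definition does not say whether qualifying two-organism cultures stay in

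*Protocol article*

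**What the plan says.** In the protocol article's Exposure section, a primary-analysis UTI needs a GP code, an antibiotic and a supporting culture. The culture rule covers three cases.

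- One organism must reach 10^8 CFU/L, with a white cell count of at least 10^8/L.
- For two organisms: "If there are two organisms grown, both must demonstrate growth of ≥1x10^8^ CFU per litre".
- For three or more: "More than two organisms will be regarded as mixed growth and thus not supportive of an UTI diagnosis".

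The text on secondary analysis 4 takes over the same rule: "both must demonstrate growth of ≥1x10^8^ CFU per litre, and more than two organisms will be regarded as mixed growth".

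Secondary analysis 1 counts differently. Its Table 2 entry reads "Yes, showing mixed bacterial growth (any descriptor for ‘mixed growth’ or >3 organisms", and the text after the table requires "a microbiology record of a urine sample with mixed bacterial growth (any descriptor for ‘mixed growth’ or >3 organisms".

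The Sensitivity and subgroup analyses section plans to explore "widening the microbiological definition of UTI to bacterial growth of a single organism" at 10^7 CFU/L or more, whatever the white cell count. The Exposure section announces the same analysis in similar terms. Neither place mentions two-organism cultures.

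**The concern.** The culture categories should fit together. Cultures that the primary rule turns away as mixed growth ought to be the ones examined in the mixed-growth analysis, and a definition called wider ought to contain the one it widens. As worded, the first does not hold and the second is unclear.

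The protocol's second objective is to compare rate ratios across ways of ascertaining UTI, and the text calls secondary analysis 1 important because the clinical meaning of mixed growth is uncertain. If one group of mixed cultures falls between the rules, that analysis does not describe the population it names. If the widened set also loses some primary episodes, a shift in the incidence rate ratio could come from the episodes added or from those removed, and the two could not be told apart. Two programmers could also code either rule differently, and the choice could end up being made after results are seen.

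**Working it through.** The plan gives no figure to reproduce here. The check applies each rule as written to the possible cultures, assuming the GP code and antibiotic are present within the window.

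| Culture | Primary | Secondary 1 | Secondary 3 | Widened, literal |
|---|---|---|---|---|
| 1 organism, ≥10^8 CFU/L, WCC ≥10^8/L | in | out | out | in |
| 1 organism, ≥10^8 CFU/L, WCC <10^8/L | out | out | out | in |
| 1 organism, 10^7 to <10^8 CFU/L, any WCC | out | out | out | in |
| 2 organisms, both ≥10^8 CFU/L, WCC ≥10^8/L | in | out | out | **out** |
| 3 organisms, ≥10^7 CFU/L, no descriptor | out, as mixed | **out** | out | out |
| 3 organisms, <10^7 CFU/L, no descriptor | out, as mixed | **out** | in | out |
| 3 organisms, ≥10^7 CFU/L, descriptor | out, as mixed | in | out | out |
| 4 organisms, ≥10^7 CFU/L | out, as mixed | in | out | out |

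**Three organisms, no descriptor.** This culture is mixed growth under the primary rule but fails the entry rule of secondary analysis 1. At 10^7 CFU/L or more it also misses secondary analysis 3 and the widened set. With a cut-off of more than two organisms in secondary analysis 1, every three-organism row enters that analysis.

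**What happens to the episode.** The Study design and Statistical analysis sections include only people with both outcome and exposure. In secondary analysis 1 there are therefore two routes:

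- If the person has another qualifying mixed-growth episode, the missed 90 days count as baseline, apart from any overlap with a risk or prerisk period.
- If it is the person's only episode, the person does not enter the analysis.

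**Size of the first route, as an illustration.** The shortest mean observation reported is 2796 days (female stroke cases). With one recognised episode, baseline is 2796 − 90 − 7 = 2699 days. One missed window makes up 90/2699 = 3.3% of it. Suppose the true rate ratio is 1.3, the value in the power statement, and that every included person has one such missed window. The baseline rate is then inflated by a factor of about 1 + 0.033 × 0.3 = 1.010, and 1.3 would be read as about 1.3/1.010 = 1.29.

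**Size of lost precision, as an illustration.** Let s be the share of mixed-growth episodes with exactly three organisms *and* no descriptor. The documents do not give s. If information is roughly proportional to the number of exposed windows, the confidence interval widens by 1/√(1 − s):

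- s = 0: 1.00
- s = 5%: 1/√0.95 = 1.03
- s = 10%: 1/√0.90 = 1.05
- s = 20%: 1/√0.80 = 1.12

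**Two organisms.** Under the literal wording, the fourth row is in the primary set and outside the widened set. If the wording is read as adding to the primary rule, the row is in both and the sets nest.

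**The case against.** The best defence is that little depends on this. The clause admitting any mixed-growth descriptor catches every three-organism culture that the laboratory labelled as mixed, so the unlabelled remainder could be close to nil. That limits the size, but it does not remove the conflict: the higher cut-off stands in both Table 2 and the text, and the text gives both cut-offs a few sentences apart.

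A reader might infer that all these episodes are counted as unexposed time. The documents do not support that, because people with no other qualifying episode are not in the analysis. Nor does the conflict cause these episodes to fall outside exposure in the primary analysis. The primary rule excludes three-organism cultures whichever cut-off secondary analysis 1 uses, and each definition leaves other kinds of UTI in baseline by design, as the protocol acknowledges for hospital-diagnosed UTI.

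A reader might also infer that the sensitivity analysis deliberately drops two-organism cultures. No sentence says so. The Exposure section speaks of widening the criteria, which can be read as adding to them. The description of secondary analysis 5 uses the same single-organism shorthand, although it is said to combine two definitions that both accept two organisms. This half is an ambiguity of wording, not a contradiction.

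Finally, the definitions are said to reflect a laboratory operating procedure that is not shown, so the documents alone do not prove which cut-off was intended. That objection stands and shapes the fix.

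**Conclusion.** The conflict over mixed growth is explicit and nothing in the article resolves it. It misplaces one narrow group: coded, treated episodes with exactly three organisms and no descriptor. Its effect on secondary analysis 1 cannot be calculated, because no counts by number of organisms are given. The bias illustration above is small even on an extreme assumption, so the likelier cost is lost episodes and an analysis that does not match its label. A 12% wider interval would need a fifth of mixed-growth episodes to be of this unlabelled kind, and nothing in the article supports that share.

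On the sensitivity analysis, the supportable conclusion is that the wording, taken literally, omits two-organism cultures that the primary rule accepts, and the plan should say whether they stay in.

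The primary definition is internally clear. The primary hypothesis and the power statement do not depend on either point. The matter is worth correcting because it changes exposure classification in one planned secondary analysis, and possibly in one sensitivity analysis, at almost no cost.

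**What to change.** 1. State one organism-count cut-off for mixed growth in the primary rule, the texts on secondary analyses 1 and 4, and Table 2, so that cultures rejected as mixed by the primary rule are the ones studied in secondary analysis 1. On the article's own primary rule this is more than two organisms or any mixed-growth descriptor. If the laboratory procedure supports a different single cut-off, use that one everywhere.
2. In both the Exposure and the Sensitivity and subgroup analyses sections, restate the widened definition as the primary definition plus single-organism cultures at 10^7 CFU/L or more, whatever the white cell count. The widened set then contains the primary set. Nesting does not require a new lower threshold for two-organism cultures.

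The cost is a few wording edits and the matching lines of the exposure algorithm, with no new data. Both should be settled before outcomes are analysed. Reporting how many cultures list exactly two and exactly three organisms, with and without a descriptor, would show whether either point mattered.
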